### Interim analyses {21b}

There are no interim analyses planned.

### Methods for additional analyses (e.g., subgroup analyses) {20b}

The study will also determine if there is a difference in the effect of inulin on the primary outcomes in terms of BMI. Subgroup analyses for the number of sites with PD ≥ 4 mm will be performed using two categories for BMI: normal BMI (< 25 kg/m^2^) or overweight/obese (≥ 25 kg/m^2^). This analysis will be conducted using an independent sample *t* test. Chi-square analyses will be performed for BOP.

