**Fig. 1 Fig1:**
[figure not shown]
Possible connection linking periodontal disease, obesity, gut dysbiosis, and low-grade inflammation. Prebiotics may restore the gut microbiome to a state of homeostasis to disrupt the connection

While the effects of inulin supplementation on periodontal disease have not been investigated, epidemiological studies have reported a significant association between intake of dietary fiber and a decreased risk of periodontal disease [21–23]. Aligned with this, higher intakes of fruits and vegetables, including inulin-containing bananas, asparagus, and leeks, were significantly associated with a lower percentage of sites with PD greater than > 3 mm after ST [3]. One intervention study provided individuals with a low-fat, high fiber test meal three times a day for 8 weeks. At the end of the intervention, participants experienced improvements in periodontal disease outcomes that included significant decreases in average PD, clinical attachment levels, and percentage of sites with BOP [24]. Of note is that participants had a body mass index (BMI) of at least 25 kg/m^2^ or demonstrated impaired glucose tolerance—two important risk factors of developing periodontal disease. Although the mechanistic action could not be established in these studies, it is clear that intake of high-fiber foods has benefits for periodontal disease. The main aim of the study is to determine if supplementation with inulin will have beneficial effects on clinical outcomes of periodontal disease in patients with periodontal disease.

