#### Anthropometric assessment

Height and weight will be measured to calculate BMI (kg/m^2^). Participants will be asked to remove their shoes and will be weighed and height will be measured to the nearest 0.1 kg and 0.1 m, respectively, using a height and weight scale (Health-O-Meter Professional; Sunbeam Products, Inc.). If certain situations prevent height and weight from being taken (COVID-19 pandemic), we will use self-reported height and weight.

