Given that obesity is a major risk factor for periodontal diseases [31], we will conduct subgroup analyses for the primary outcomes in which participants are categorized as either having a BMI that is classified as normal or overweight/obese. A systematic review with a meta-analysis reviewed the efficacy of ST among obese and non-obese participants [32]. The meta-analysis showed comparable outcomes in terms of in PD and clinical attachment loss between obese and non-obese subjects. However, in two of the five studies included, participants with obesity had a smaller reduction in mean PD from baseline to follow-up. The other three studies showed comparable clinical periodontal condition in both obese and non-obese patients. The authors could not conclude if ST had a different effect in obese compared to non-obese participants with chronic periodontitis because of these conflicting results; however, they did report that serum IL-6, tumor necrosis factor-α, and leptin levels were more elevated in the obese compared to non-obese patients at both baseline and follow-up. This finding can be explained by the fact obesity results in a greater number of adipocytes and adipocytes that produce hormones and pro-inflammatory cytokines, including those found elevated in the studies, which relate to low-grade systemic inflammation [33]. Inulin supplementation at 10 g/day in patients with type 2 diabetes mellitus has demonstrated the ability in decreasing weight and BMI with significant decreases in serum high sensitivity-CRP, TNF-α, and LPS [34]. We anticipate that inulin may be able to attenuate obesity-related inflammation and as a result, overweight/obese participants may demonstrate greater reductions in PD and BOP than non-obese participants. This follows the hypothesis that systemic inflammation is one of the factors linking obesity to periodontal disease.

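### Whether inulin's effect differs by BMI is to be judged only from a split at 25 kg/m² with t tests and chi-square; a treatment × continuous baseline BMI term would use more of the available information at almost no cost

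*Protocol article*

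**What the plan says.** The section Methods for additional analyses {20b} states the aim: "The study will also determine if there is a difference in the effect of inulin on the primary outcomes in terms of BMI". It then fixes the method. For probing depth, the subgroup work "will be performed using two categories for BMI: normal BMI", meaning under 25 kg/m², is set against one pooled group of everyone at 25 or more. The named test is a t test for independent samples, and BOP gets chi-square. No treatment-by-BMI term is mentioned.

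Under Anthropometric assessment, "Height and weight will be measured to calculate BMI", with self-report as the fallback when measurement is prevented. Each participant therefore has a BMI value, not just a category.

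The Discussion opens its rationale with "Given that obesity is a major risk factor for periodontal diseases", and says participants will be classed as normal or overweight/obese. Its evidence is a meta-analysis of obese against non-obese patients, and its mechanism is that "obesity results in a greater number of adipocytes and adipocytes that produce hormones and pro-inflammatory cytokines". It then predicts that "overweight/obese participants may demonstrate greater reductions in PD and BOP than non-obese participants". A later paragraph predicts a greater response in overweight/obese participants.

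The Background, after Fig. 1, describes a high-fibre intervention study whose "participants had a body mass index (BMI) of at least 25 kg/m^2^ or demonstrated impaired glucose tolerance", and calls both of these important risk factors for periodontal disease.

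**The concern.** The question is whether a treatment effect varies with a quantity recorded on a continuous scale. Reducing that quantity to two groups treats BMI 25.1 and BMI 40 as the same and 24.9 and 25.1 as different. If modification rises with BMI, or sets in at obesity, pooling overweight with obese participants dilutes the contrast.

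The planned contrast is also not quite the one argued for. The evidence and mechanism in the Discussion are about obesity, and one sentence there sets overweight/obese participants against non-obese ones. Overweight participants who are not obese belong to both sides of that comparison.

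Nor do the named tests answer the question. A t test of inulin against placebo within each BMI group gives two separate results, not a test of their difference. A t test between BMI groups would ignore treatment.

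At stake is the conclusion on BMI that the Discussion anticipates reporting. A null result could be misread as showing that BMI does not matter, and a significant result in one group only could be misread as showing that it does. The primary comparison is not touched.

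**Working it through.** **Inputs from the article, section Sample size for full trial.** SD of the change 21 sites; mean change 81 against 91, so a difference of 10; 80% power; alpha 0.05; 71 per group evaluable, N = 142. Allocation is 1:1.

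**Reproducing the plan's figure.** A two-sided two-sample t test with difference 10, SD 21 and 71 per group has 80.4% power; 70 per group gives 79.9%. The stated 71 reproduces. The article gives no figure for the BMI analysis.

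**Assumed.** Normally distributed BMI, with p the share below 25. Mean BMI 26–30 with SD 4.5–6 gives p of about 0.20 to 0.41; p = 0.50 is added as the case most favourable to the cut.

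**Step 1: information kept by the cut if modification is linear in BMI.** This is the squared correlation between BMI and the indicator BMI ≥ 25: φ(z_p)² / [p(1 − p)], where φ is the standard normal density at the p-quantile. At p = 0.20: 0.280² / 0.16 = 0.49. At p = 0.50: 0.399² / 0.25 = 0.64.

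**Step 2: power for a difference in effect of 10 sites between the two BMI groups.**
- SE of the two-category interaction: 2 × 21 / √[142 p(1 − p)] = 3.525 / √[p(1 − p)].
- z for the cut: 10 / SE. z for continuous BMI under the same linear truth: that value divided by the correlation, the square root of the share kept.
- Power: Φ(z − 1.96).

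| Share below 25 | Kept | Lost | SE (sites) | Power, cut | Power, continuous |
|---|---|---|---|---|---|
| 0.50 | 64% | 36% | 7.05 | 29% | 43% |
| 0.41 | 62% | 38% | 7.17 | 29% | 42% |
| 0.35 | 60% | 40% | 7.39 | 27% | 41% |
| 0.30 | 58% | 42% | 7.69 | 25% | 40% |
| 0.25 | 54% | 46% | 8.14 | 23% | 39% |
| 0.20 | 49% | 51% | 8.81 | 21% | 37% |

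At 80% power the two-category interaction detects 2.80 × SE, or about 20 sites (p = 0.50) to 25 sites (p = 0.20). That is at least twice the whole assumed effect of 10.

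**Step 3: other shapes of modification** (p from 0.20 to 0.41, scaled so that the correct cut would have 80% power).
- Step at BMI 30: the 25 cut keeps 16–26% of the information and has 20–30% power; a linear BMI term keeps 48–64% and has 49–61%.
- Step exactly at 25: the planned cut has 80% power, continuous BMI 50–60%.

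**Step 4: why separate within-group tests do not answer the question.** Take p = 0.25 and the same 10-site effect in everyone, so no modification. Group sizes per arm are about 17 and 53, with power 27% and 68%. The chance of a significant result in the overweight/obese group and none in the normal group is 0.68 × (1 − 0.27) = 0.50. At p = 0.50 it is 0.50 × 0.50 = 0.25.

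**The case against.** Several points on the other side stand.

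- **The cut is not arbitrary.** The Background ties a BMI of at least 25 to the one fibre intervention study cited and calls it a risk factor. The Discussion's main hypothesis is normal against overweight/obese, which is what {20b} plans. A reader might infer that the protocol gives no reason for 25; that goes too far. But the Background passage describes another study's participants, who could also qualify by impaired glucose tolerance. It is no evidence that the effect steps at 25.
- **No graded relation is stated.** A reader might take the rationale to be dose-response. The text does not say so; linearity is an analyst's assumption, and at this sample size a few extreme BMIs could carry leverage.
- **The information loss is not a property of the plan.** A flat statement that 40–50% is discarded would not be supported. The figure depends on an unreported BMI distribution and on linearity, and is zero under a step at 25.
- **Larger power gains can be produced, but only with steep modification.** Letting the effect average 10 sites and be zero at BMI 22 gives 89% against 71%, or 57% against 32%, depending on the BMI distribution. That slope makes inulin worse than placebo below BMI 22 and implies 13–18 sites between the groups.
- **BMI may be self-reported.** The resulting noise affects either approach.
- **This is an unpowered additional analysis.** Conventional categories are easy to read, and no primary estimate changes.

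None of this justifies relying on the two categories alone, without an interaction term, to decide whether the effect differs.

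**Conclusion.** The point holds as an inexpensive improvement to an exploratory analysis. {20b} asks an effect-modification question and answers it with a two-way split and tests that do not compare the effects.

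Under normal BMI, linear modification and 20–50% of participants below 25, the split costs about 36–51% of the information. For a 10-site difference between groups, power is about 21–29% with the split and 37–42% with continuous BMI (20–41% below 25). These figures use 142 evaluable participants. The recruitment target of 170 less the planned 20% leaves 136, which lowers them to about 20–28% and 35–41%.

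A reader might conclude that the change makes the BMI question answerable. It does not: both versions are underpowered for a difference as large as the whole assumed effect, and the result should be presented as exploratory. Nor does the point bear on the validity of the primary comparison.

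Separately, the Discussion's contrast of overweight/obese with non-obese does not match the two groups in {20b} and needs aligning.

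**What to change.** In {20b}:

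1. Make the test of effect modification a model for the change in number of sites with PD ≥ 4 mm containing treatment, baseline (Visit I) BMI as a continuous covariate, and treatment × BMI. Use the corresponding model for BOP.
2. Report the estimated inulin effect with a 95% CI at a few prespecified BMI values, for example 22, 27 and 32 kg/m².
3. Keep the < 25 and ≥ 25 results as descriptive summaries.
4. Label the analysis exploratory.

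In the Discussion, reword the prediction so that overweight participants fall on one side only, consistent with {20b}.

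The cost is a sentence or two of analysis wording, with no new data, visits or participants. The downside is the assumption of linear modification and lower power if the effect steps exactly at 25; the retained descriptive categories partly cover that case.

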#### Sample size for full trial

The number of sites with probing depths ≥ 4 mm was used to determine sample size, as ST has been shown to reduce BOP to minimal levels to the point where an adjunct could not increase the effectiveness [3]. Previous literature has reported the mean change in number of sites with probing depths ≥ 4 mm from baseline to an average follow-up of 10.86 weeks is a mean of 81 with a standard deviation of 21 [3]. It has been shown that a high fiber diet can result in a 4% decrease in average PD though these participants were not diagnosed with periodontal disease and were not undergoing treatment with ST [24]. We believe it is reasonable to estimate that participants who are suffering from this disease and have deeper probing depths will experience a greater reduction in PD ≥ 4 mm in combination with ST (10%), as baseline PD is positively associated with follow-up PD [3]. Thus, the estimated mean change in the number of sites with probing depths of ≥ 4 mm is 91. Using a power of 80% and an alpha of 0.05, the total number of participants needed per group is 71. A 20% drop-out rate is estimated; the sample size for the full trial is 85 per group or a total of 170 participants. The sample size needed for the full trial was estimated using a statistical software (G*Power 3.1).

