This study will contribute to a better understanding of the role of inulin, a type of prebiotic, and periodontal disease. To our knowledge, no direct intervention with prebiotic supplementation to support the effectiveness of ST for periodontal disease has been conducted. Though, there is evidence that a higher intake of dietary fiber supports periodontal health. Dietary fiber may act as a mechanical force on the dental surfaces to aid in the shedding of the periodontal-associated pathogens in the microbial biofilm [35]. We will determine if a supplement can still be effective for periodontal health, given the lack of mechanical force needed for digestion of the inulin supplement to be provided.

This unique study design allows us to measure the response of inulin prior to and after sanative therapy. We can determine if inulin can improve periodontal biomarkers alone and if inulin can be considered an adjunct to ST. Salivary biomarkers are likely to change prior to improvements in clinical outcomes, which is why we are measuring salivary biomarkers and periodontal pathogens but not clinical outcomes at Visit II. The first 4 weeks of the intervention prior to ST will be used to assess the response of inulin alone; we predict that inulin supplementation may be able to decrease salivary markers of inflammation and periodontal-associated pathogens. The remaining 10 weeks will compare ST to ST and inulin supplementation. It is hypothesized that the inulin group will have a greater reduction in the number of sites with PD ≥ 4 mm and for the percentage of sites with BOP. Further, the subgroup analyses are anticipated to show that the response is greater in participants who are overweight/obese.

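### The plan asks whether the effect of inulin differs by BMI, but the t and chi-square tests it names do not test a difference in effect between BMI groups

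*Protocol article*

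**What the plan says.** The section on additional analyses {20b} sets the question: "The study will also determine if there is a difference in the effect of inulin on the primary outcomes in terms of BMI". The PD subgroup analyses "will be performed using two categories for BMI: normal BMI" (below 25 kg/m²) and overweight/obese (25 kg/m² or above). For the test, it says "This analysis will be conducted using an independent sample" t test. For bleeding, "Chi-square analyses will be performed for BOP".

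The Discussion gives the expected answer: "the subgroup analyses are anticipated to show that the response is greater in participants who are overweight/obese". An earlier Discussion paragraph gives the rationale, that inulin may dampen obesity-related inflammation.

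Neither {20b}, the main statistical methods section {20a} nor the Discussion names a treatment-by-BMI interaction or homogeneity test. They also do not say which two groups the t test compares, or what result would count as a difference between BMI groups.

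**The concern.** Whether an effect differs between two BMI groups is a question about four cells: inulin and placebo, in each BMI group. The estimate needed is the effect in one stratum minus the effect in the other. An independent-sample t test makes one two-group comparison, so there are two ways to read the plan.

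- **Inulin against placebo within each stratum.** This gives two p-values and no test of whether the two effects differ. One significant and one non-significant result is weak evidence of a difference, because each stratum has far less power than the whole trial.
- **Normal BMI against overweight/obese.** This mixes BMI as a predictor of response to sanative therapy with BMI as a modifier of the inulin effect.

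The chi-square tests have the same limitation. At stake is a pre-announced claim that overweight/obese participants benefit more. If that group is the larger one, its test has more power, so the expected pattern is favoured even when the effect is the same in both groups.

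**Working it through.** **Inputs from the protocol (Sample size for full trial).** Control change "is a mean of 81 with a standard deviation of 21"; inulin change 91, so the planned difference is 91 − 81 = 10 sites; "Using a power of 80% and an alpha of 0.05, the total number of participants needed per group is 71"; 85 per group after a 20% dropout allowance.

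**Assumptions.** The protocol does not give the BMI split, so 50:50 to 20:80 (normal : overweight/obese) is shown. Analysed numbers per arm run from 68 (85 × 0.80) through 71 to 85. The assumed reading rule is that a difference is inferred when exactly one stratum has two-sided p < 0.05.

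**Step 1: reproduce the plan's figure.** Standardised difference 10/21 = 0.476. The two-sided noncentral-t calculation gives 71 per group (power 80.4%), as stated. A one-sided test would need 55, so the plan is two-sided.

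**Step 2: within-stratum tests, same true effect in both strata.** With stratum powers p₁ (normal) and p₂ (overweight/obese):

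- P(exactly one significant) = p₁(1 − p₂) + p₂(1 − p₁)
- P(only overweight/obese significant) = p₂(1 − p₁)

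At 68 per arm split equally (34 per arm per stratum), each power is 0.49. Disagreement is 2 × 0.49 × 0.51 = 0.50, and the expected pattern alone is 0.49 × 0.51 = 0.25.

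Results for a common 10-site effect:

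| Per arm | Split | p₁ | p₂ | Exactly one significant | Only overweight/obese |
|---|---|---|---|---|---|
| 68 | 50:50 | 0.49 | 0.49 | 50% | 25% |
| 71 | 50:50 | 0.51 | 0.50 | 50% | 24% |
| 71 | 30:70 | 0.33 | 0.66 | 55% | 44% |
| 71 | 20:80 | 0.23 | 0.71 | 61% | 55% |
| 85 | 50:50 | 0.58 | 0.59 | 49% | 25% |
| 85 | 30:70 | 0.39 | 0.73 | 55% | 44% |
| 85 | 20:80 | 0.27 | 0.79 | 63% | 57% |

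**Step 3: other true effects.** A common 5-site effect gives disagreement in 27–33% of trials over the same range. No inulin effect gives 2 × 0.05 × 0.95 = 9.5%.

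**Step 4: the other reading.** Suppose the t test compares BMI groups within the inulin arm (71 participants) and BMI does not modify the effect. The false-positive rate is 5% if BMI is not prognostic. If BMI alone shifts the change by 5 sites, it is 17% (50:50) or 15% (30:70). With a 10-site shift, it is 51% or 44%.

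**Step 5: an interaction test.** In a four-cell linear model (40,000 simulated trials per setting), a treatment-by-BMI test at two-sided 0.05 gave false declarations in 4.8–5.2% of trials. This covered a common effect of 0 or 10 sites, 71 or 85 per arm, and splits of 50:50 and 30:70.

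Its standard error is 21 × √(2/a + 2/b), where a and b are the numbers per arm in the two strata. At 71 per arm:

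- 50:50: 21 × √(2/36 + 2/35) = 7.05 sites
- 30:70: 21 × √(2/21 + 2/50) = 7.72 sites

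Power for a 10-site difference in effect is therefore about 29% and 25%. A power of 80% needs a difference of about 2.80 × 7.05 = 20 to 2.80 × 7.72 = 22 sites.

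**BOP.** The protocol gives no bleeding rates, so no corresponding figure can be calculated.

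**The case against.** **The rates are conditional.** A reader might infer that the plan will falsely declare a BMI difference about half the time. The protocol does not support that as a general statement. It never says that a difference will be read from one stratum being significant and the other not; it only anticipates a larger response in one group. The 49–63% also needs inulin to work by the full 10 sites, equally in both strata, and the protocol itself notes that no randomised trial has tested inulin with sanative therapy. At smaller common effects the rate falls, to 9.5% with none. For the directional pattern that the authors expect, it is about 25% at an equal split, not half. The figures concern PD sites only. All of this stands and limits the size of the claim, but it does not make the named tests answer the question.

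**It could be left to an analysis plan.** This would be fair if the section were silent. It is not: it fixes the cut-point and the tests, and the article describes itself as the full protocol. The authors already plan a treatment-by-time term for the biomarkers, so a factorial model is not foreign to their approach.

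**Height precision.** A reader might add that the anthropometry section ("height will be measured to the nearest 0.1 kg and 0.1 m, respectively") would misclassify BMI and make matters worse. The 0.1 m looks like a unit slip to be checked separately. Any misclassification rate needs height and BMI distributions that the protocol does not give, and rounding unrelated to the allocated arm would blur the groups, not create a false difference between them. It is no part of this point.

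**Conclusion.** The point holds as a mismatch between question and method: the protocol asks about effect modification by BMI and names tests that do not assess it under either reading. That conclusion needs no numerical assumption.

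The error rates in the working illustrate one plausible way of reading the results. They rest on the planned SD of 21, the assumed BMI splits and the unstated significant-in-one-only rule, and should be quoted only with those conditions. The matter affects a pre-announced subgroup claim, not the primary comparison. It should be corrected before analysis.

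**What to change.** Replace the subgroup tests in {20b} with one model per primary outcome, fitted in all analysed participants:

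- **PD sites:** a linear model for the change in number of sites, with the baseline value, treatment, baseline BMI group and treatment × BMI group.
- **BOP:** a logistic-type model with treatment, baseline BMI group and treatment × BMI group.

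State that any claim of effect modification rests on the interaction estimate with its 95% CI, and that stratum effects are shown descriptively with confidence intervals. Label the analysis exploratory because of the low interaction power, and say that a non-significant interaction will not be read as evidence that the effect is the same in both groups.

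The cost is a change of wording in the protocol and analysis plan. BMI, PD and BOP are already collected at baseline, so no new data or participants are needed.
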